### Data management

To give HSAs an organic user experience, identifiable data was entered into the SL eCCM App. Once the record was saved, patient-identifiable information entered (i.e., child and parent name, physical address) was automatically removed and date of birth was transposed into age (in months). Patient data was held within the SL eCCM App in SQLite database tables until the App was synced with the SL central database, when patient records were automatically removed from the App. De-identified patient data held in database tables within the App was encrypted using secure, 256-bit AES SQLCipher technology. HSAs synced the SL eCCM App with the server from village clinics, or other community locations with a WIFI or data network. Patient records were transmitted by HSAs daily, or as soon as they were able to reach an area with connectivity. Secure Sockets Layer (SSL) technology was used to protect data during transmission from the SL eCCM App to the SL central database, which was managed through a website created to provide an infrastructure for administrative support during the trial (e.g., creating HSA accounts). This website was developed using Java Server Pages (JSP), Bootstrap, JQuery, HTML 5.0 and CSS 3.0. SQLCipher is the technology adopted for provisioning data encryption. SQLCipher is an open-source library that provides transparent, secure, 256-bit AES encryption of SQLite database files. SQLCipher has been adopted as a secure database solution by many commercial and open-source products, making it one of the most popular encrypted database platforms for mobile applications. The SL database is hosted within the AWS data center in Ireland, which is the European base for AWS service provision. User-authentication controls restricted access to the SL eCCM App and SL central database to authorized trial personnel.

The quality of data collection in this trial was contingent upon the completeness and accuracy of patient records at village clinics and higher-level health facilities. To ensure that all available data was abstracted from patient records at these sites, CRF and PCQ Forms were reviewed for completeness by a member of the local study team prior to data entry. De-identified CRF and PCQ data was double entered into the Health Insurance Portability and Accountability Act (HIPAA)-compliant Research Electronic Data Capture (REDCap) system, which was managed by the local trial team in Malawi and monitored remotely by the trial sponsor. REDCap database was set up with double-data entry and validation rules to identify and manage data discrepancies. Data entered into REDCap was reviewed continually during the trial. Missing or inconsistent data was identified and data verification requests generated by the sponsor institution to resolve discrepancies. Individual characteristics of CHWs (e.g., education level) have been associated with enhanced performance in resource-poor settings [49]. Location of village clinics and higher-level health facilities may also influence the quality of medical reporting in patient records and thus the data that is available to be abstracted for this study. HSAs operating in more urban areas may have better access to training and supervision. Urban regions with better infrastructure might have more standardized and organized reporting systems, or conversely, less rigorous procedures because of higher patient volumes. As the factors driving missing data (in addition to attrition of HSAs) in this study risk biasing observed data collected, we cannot assume that data will be missing at random. Therefore, missing data will not be imputed [50]. Upon trial completion, the percentage of missing data between control and intervention phases will be compared. We will use a logistic model to assess whether any covariates significantly predict dropout rates; differential dropout will be assessed. Non-outcome variables will be interpolated to improve multivariate models if needed.

### Confidentiality

Patient records entered into the SL eCCM App during the intervention are identified using a unique, five-digit, study ID number and HSAs are identified from a unique, four-digit number (as pre-populated on completed consent documents). A link between participant ID number and participant names (children and HSAs) is stored in a separate electronic file and will be broken as soon as it is practical to do so. Since a single HSA is typically assigned to each village clinic in Malawi, disclosure of study sites would constitute the release of identifiable data. Therefore, to protect participant’s identity, the list of included village clinics will not be made available. Audio files of interviews will be uploaded and transcriptions stored onto a password-protected computer. Participant identifiers accidentally disclosed during interviews will be removed during transcription and replaced with generic terms (e.g., personal names will be replaced with “a colleague” or “family member”). Participant quotes used in any material resulting from this trial will be protected using their unique ID number. All original study documents (i.e., consent documents, CRFs, PCQs) are stored securely at the local coordinating institution in Malawi (LIN) with access restricted to authorized personnel. After trial closure these trial documents are to be archived locally for 6 years in accordance with the University of Washington’s Human Subjects Division and COMREC’s requirements, and will only be made available under exceptional circumstances (e.g., audit). After verification of data accuracy, electronic datasets will be locked and stored on encrypted institutional networks.

#### Post-trial care

After trial completion, children aged under 5 years presenting to village clinics were to continue treating children aged under 5 years according to standard practice (paper-CCM only).

#### Statistical/analysis methods

Primary outcome data will be evaluated using pairwise comparisons during the control and intervention periods. Analyses will be conducted at the level of the HSA, taking into consideration the number of index visits that occurred during each period, and will include descriptive statistics relating to each outcome (i.e., referral, re-consultation and hospitalization rates); tests of differences by control/intervention period, and multivariate modeling to allow for adjustment of potential confounding factors within each period. Bivariate descriptive statistics will present proportions for categorical variables or means/standard deviations for continuous and categorical data (respectively), for control/intervention periods. Measures of change will be calculated and two-proportion z-tests or chi-square tests will be used to measure unadjusted differences (depending on test assumptions met). We will conduct multivariate analysis using linear regression to evaluate change in outcomes adjusted for composition of children at each HSA by age, gender, symptoms, location (urban/rural) and proximity to the nearest higher-level health facility. For these models, assumptions will be tested, transformations of variables will be made if needed, and a-priori confounders will be evaluated for inclusion in models. Effect modification will be tested by interactions with age and gender. A secondary analysis will be done at the level of the child adjusting for HSA as a cluster variable. Potential confounders and effect modifiers will also be tested in these models. Data analysis and reporting will be conducted with Consolidated Standards of Reporting Trials (CONSORT) [51].

A cost-consequence analysis will be conducted to report the costs and consequences under the control and intervention. All costs of seeking and receiving care for the control and intervention groups will be calculated separately in a disaggregated way at the household level. Direct costs (e.g., out-of-pocket payments and transportation costs), indirect costs (e.g., costs of parent/caregiver productivity loss) and consequences (e.g., hospitalization days) collected through the PCQ will be compared between parents/caregivers enrolled in the control and intervention phases.

Audio-recordings from interviews will be transcribed and translated into English during data collection. It is anticipated that audio-recordings will take some time to be translated and transcribed, making theoretical sampling impractical. Therefore, data synthesis will commence as soon as it is practical to do so. Appropriate qualitative synthesis techniques will be employed, and reporting will adhere to the consolidated Criteria for Reporting Qualitative research (COREQ) [52]. Qualitative data will be triangulated with primary outcomes to contextualize quantitative findings. Qualitative software package NVivo 10 will be used to organize the data.

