## Methods/design

### Trial design

This is a pragmatic, stepped-wedge cluster-randomized trial assessing the added value of the SL eCCM App (used with paper-CCM) on referral, re-consultation and hospitalization rates of children aged under 5 years, within 7 days of the index visit. This design was chosen due to insufficient human resources to deliver the intervention to all clusters simultaneously [32] and local advice that withholding the intervention to some clusters may negatively affect participation. We aimed to recruit 102 HSAs and collect data on 8000 children from village clinics across two districts in Northern Malawi between July 2016 and February 2017. HSAs were grouped into six geographic-based clusters. Training workshops were conducted prior to the control (paper-CCM) and intervention (paper-CCM + SL eCCM App) in assigned clusters. Clusters were randomly assigned to the timing of crossover from the control to the intervention [32] for covariate equipoise between phases [33]. A nested qualitative study explored HSA and caregiver perceptions of caregiver adherence to urgent referral recommendations; a cost evaluation investigated the financial and time-related costs to caregivers of seeking subsequent health care for their child after the index visit. Figure 1 shows the trial flow chart; Fig. 2 the trial design (before randomization) and Fig. 3 the Standard Protocol Items: Recommendations for Interventional Trials (SPIRIT) Figure. This protocol adheres to the SPIRIT 2013 Statement for clinical trial protocols (Additional file 1) [34].

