## Assignment of interventions

### Randomization, allocation and blinding

HSAs were stratified by geography into six clusters by the local study team and each cluster was given a number between 1 and 6 Using computer-generated simple randomization techniques, each of the six clusters was randomized to the sequence and timing at which they crossed over from the control to the intervention (Fig. 3) [39]. Clusters were randomized once allocated to geographic clusters. Caregivers and their child were allocated to the control or intervention by chance, depending on the time that they presented to village clinics. Due to the nature of the intervention, neither trial participants nor the trial team were able to be blinded to assignments.

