### Sample size

We planned to recruit a total of 102 HSAs. Our sample size estimation is based on change in proportions of the primary outcomes expected pre and post intervention. Assuming an alpha of 0.05, 97 HSAs would provide 80% power for a minimum detectable rate of change between 6 and 7% in referral, re-consultation and hospitalizations (one-sided test). We assumed a 1% urgent referral rate, based on the proportion of children identified as needing to be urgently referred at clinics in a previous study conducted in Malawi [11]. As an urgent referral rate of 8% has been estimated as a reasonable consensus referral rate at clinics in sub-Saharan Africa [43, 44] that are correctly adhering to IMCI, we assumed the addition of the SL eCCM App could improve urgent referral rates close to this estimate; a 6–7% change between the control and intervention was, therefore, a conservative estimate of this assumption. Given the short trial duration and potential of perceived elevated status through smartphone ownership in this setting [45], we did not expect many HSAs to drop out. We believed that recruiting 102 HSAs would be sufficient to accommodate potential dropout, to ensure we achieved our desired sample size. Power calculations were computed using the “Power and Sample Size” option in Stata v. 13 (StataCorp, College Station, TX, USA) [46] which is appropriate for rates, specifically “*longitudinal studies, where the same cases serve as their own controls over time*” [47].

A total of 300 parents/caregivers whose children were referred to a higher-level facility or re-consulted at a village clinic completed the PCQ. It was estimated that approximately 600 children would be eligible for referral to a health care facility assuming: a 1% referral rate among 4000 children in the control group (*n* = 40), a 7–8% referral rate (change 6–7% from the initial 1% referral rate) among the same number of children in the intervention group (*n* = 300) and a 6–7% under-referral rate in the control group (*n* = 260). Considering the challenges in identifying those who were referred but did not present at a health care facility, or those who were not referred but did visit a health care facility or represented at a village clinic, and the possible withdrawal or loss to follow-up of parents/caregivers, it is estimated that at least half (*n* = 300) of the eligible cases will be followed up as part of the cost evaluation.

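### The primary comparison and every named model omit calendar time, so a net trend during recruitment that the listed covariates do not carry is reported as an App effect

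*Protocol article*

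**What the plan says.** The Trial design section describes a stepped wedge: "Clusters were randomly assigned to the timing of crossover from the control to the intervention". The randomization section adds that "each of the six clusters was randomized to the sequence and timing at which they crossed over from the control to the intervention". The Control and Intervention sections give each cluster 2 to 7 weeks on paper-CCM and then 2 to 7 weeks with the App added. Control always comes first.

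Under Statistical/analysis methods, the primary analysis is fixed in one sentence: "Primary outcome data will be evaluated using pairwise comparisons during the control and intervention periods". It continues: "Analyses will be conducted at the level of the HSA, taking into consideration the number of index visits that occurred during each period". For the crude comparison, "two-proportion z-tests or chi-square tests will be used to measure unadjusted differences". The linear regression is "adjusted for composition of children at each HSA by age, gender, symptoms, location (urban/rural) and proximity to the nearest higher-level health facility". Finally, "A secondary analysis will be done at the level of the child adjusting for HSA as a cluster variable". Calendar week, step and period are named in none of these analyses.

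The Sample size section follows the same logic: "Our sample size estimation is based on change in proportions of the primary outcomes expected pre and post intervention".

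**The concern.** In a stepped wedge, control data come on average from earlier calendar time than intervention data. Randomizing the order of crossover does not balance time between the two conditions. What it provides is clusters that are still in control while others have switched, so that time can be estimated and removed. The stated analysis does not use that information, because each HSA is compared only with its own earlier self or all periods are pooled.

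The outcomes concern acute childhood illness, and the Trial status section has recruitment opening on 24 October 2016 and follow-up data collected by 3 February 2017. A flat trend in presentation, severity or referral habits cannot be presumed over such a period. The Background hypothesis is that referral rises while re-consultation and hospitalization fall, so one trend would push the apparent result in opposite directions across the outcomes. The limitations in the Discussion do not mention time.

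**Working it through.** **1. The plan's own figure.** The Sample size section gives 97 HSAs for 80% power, one-sided alpha 0.05, and a change of 6 to 7 points from 1%. A paired formula with all change in one direction is n = [(1.645·√d + 0.842·√(d − d²)) / d]².
- d = 0.0625: (0.411 + 0.204)/0.0625 = 9.84, and 9.84² = 96.8, so n = 97.
- d = 0.06 gives 101; d = 0.07 gives 87.

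An independent two-proportion formula gives 131 per group (1% v 7%) or 108 (1% v 8%) and does not reproduce 97. The match is not unique, because the article does not state the discordance. It does fit a pure before-after design, and the later steps do not depend on it.

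**2. The calendar gap.** Assume a common 9-week calendar with crossover after week c, where c = 2, 3, 4, 5, 6, 7. This fits the stated 2-7 weeks in each condition, but the design figure is not shown.
- Mean control week = (c + 1)/2.
- Mean intervention week = (c + 10)/2.
- Difference = 9/2 = 4.5 weeks, whatever c is.

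A linear trend of b points per week therefore adds 4.5b to every HSA's paired difference. The whole trend from week 1 to week 9 is 8b, so the share absorbed is 4.5/8 = 56%. Pooled over clusters, the control weeks average 83/27 = 3.07 and the intervention weeks 187/27 = 6.93, a gap of 3.85 weeks for the z or chi-square test. Training breaks are ignored; they would widen the gap.

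**3. Non-linear trends.** Take a trend that climbs evenly to week 5 and falls back evenly, with range 1. The six cluster differences are +0.41, +0.29, +0.125, −0.125, −0.29 and −0.41, which average zero. Only the net directional part of a trend biases the average.

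**4. False-positive rates with no App effect.** Assumptions: 6 clusters of 17 HSAs, 10 children per HSA-week, cluster SD 0.3 and HSA SD 0.5 on the log scale, mean starting rate 1%, linear rise, paired HSA-level test, one-sided 5%.

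| Relative rise over 9 weeks | Rejection rate | False effect (points) |
|---|---|---|
| none | about 5% | 0 |
| 25% | about 15% | 0.25 × 0.5625 = 0.14 |
| 50% | about 30% | 0.50 × 0.5625 = 0.28 |
| 100% | about 64% | 1.00 × 0.5625 = 0.56 |

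These inputs imply 6 × 17 × 10 × 9 = 9,180 children against the planned 8,000. A separate simulation at 8000/(102 × 9) = 8.7 children per HSA-week, with between-HSA SD set at 30% of the base rate, gave 58% (paired) and 55% (pooled z) for a one-point rise from 1%. Adding cluster and week effects brought rejection back to 4.5-5.5% under every trend tried, with a mean estimate of about zero.

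**5. Scale against the target.** To imitate the full design effect, a linear trend would need 6/4.5 = 1.3 to 7/4.5 = 1.6 points per week, or about 10.7 to 12.4 points over recruitment.

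**6. Cost of adjusting for time.** At a 1% rate, HSA intraclass correlation 0.02 and 10 children per HSA-week, the generalized least squares standard error is 0.216 points without week effects and 0.353 with them: (0.353/0.216)² = 2.67 times the variance. With cluster fixed effects and equal cluster-week weights, the information falls from 11.56 to 3.89, a factor of 2.97. The detectable difference at 80% power is (1.645 + 0.842) × 0.353 = 0.9 points. A harsher case (7% rate, cluster-by-week SD 30% of the rate) gives a standard error of 1.40 and 2.487 × 1.40 = 3.5 points.

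**The case against.** The strongest reply is that the article promises a full statistical analysis plan before analysis, and that a period term could be given there. The methods section also says that a-priori confounders will be evaluated for inclusion. This limits the charge to what the article names, but does not answer it. The article states the primary comparison, its tests and its covariates; within an HSA, a linear trend shifts every paired difference by the same amount. An additional listed confounder would not repair that comparison, so the later plan would have to replace it.

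A reader might infer that any calendar trend passes in full into the App effect, with no correction at all. The document does not support that reading, for three reasons.
- A trend symmetric about the middle of recruitment cancels on average across the staggered steps, and a linear one passes through at 56%, not 100%.
- The regression adjusts for symptoms and age, so drift in case mix that works through them would be partly removed.
- The false effects are small beside the design effect; a trend alone would have to be very steep to produce a 6-7 point change.

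It is also fair that the article gives no trend size, so the rejection rates illustrate sensitivity and do not predict what happened.

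**Conclusion.** The concern holds in this limited form and should be corrected before analysis. The stated primary analysis and all named models omit calendar time in a design where intervention always follows control. A net directional trend outside the listed covariates is therefore attributed to the App for all three outcomes. The 4.5-week gap and the 56% share rest on the assumed common 9-week calendar; the rejection rates rest also on the assumed trends, cluster sizes and variance components. The danger is a statistically significant but small spurious difference, or a masked small real one. It is not that a modest trend could imitate the 6-7 point target. Recruiting more children would not help: it narrows the interval around a biased value.

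**What to change.** Make the primary analysis a stepped-wedge model on child-level or HSA-week data, with:
- an intervention indicator;
- fixed effects for calendar week or step;
- random effects for geographic cluster and HSA, with cluster-by-week where it can be estimated;
- small-sample or permutation inference suited to six randomized clusters. With one cluster per step there are 6! = 720 possible orders.

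Report the period-adjusted effect with its confidence interval as the primary result for each outcome, and keep the crude control and intervention proportions as description. Restate the power statement in the Sample size section to match, since it rests on pre-post change.

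No new data should be needed, because a 7-day outcome window already requires the index visit date. The cost is precision: about 2.7 to 3 times the variance, more with cluster-by-week variation. The small-sample correction widens the interval further, by an amount not calculated here. On the figures above, the detectable difference of about 0.9 points, or 3.5 in the harsher case, stays below the 6-7 point target.

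### Six geographic clusters were randomised, but no planned analysis uses the randomised cluster, so standard errors are unprotected against change shared within a cluster and are likely too small

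*Protocol article*

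**What the plan says.** On randomisation, the protocol article (Randomization, allocation and blinding) states "HSAs were stratified by geography into six clusters by the local study team" and then that "each of the six clusters was randomized to the sequence and timing at which they crossed over from the control to the intervention". Trial design agrees ("HSAs were grouped into six geographic-based clusters") and sets the scale: "We aimed to recruit 102 HSAs and collect data on 8000 children from village clinics".

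On analysis, the Statistical/analysis methods section fixes the unit: "Analyses will be conducted at the level of the HSA, taking into consideration the number of index visits that occurred during each period". Three tools follow:

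- Unadjusted tests: "two-proportion z-tests or chi-square tests will be used to measure unadjusted differences".
- Adjusted model: "We will conduct multivariate analysis using linear regression to evaluate change in outcomes adjusted for composition of children at each HSA". Its covariates are case mix, urban or rural location, and distance to a higher-level facility.
- Secondary analysis: "A secondary analysis will be done at the level of the child adjusting for HSA as a cluster variable".

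The Sample size section bases 80% power on 97 HSAs, one-sided at 0.05, with each case serving as its own control. It gives no intracluster correlation or design effect.

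**The concern.** A cluster-randomised comparison is protected by the units that were randomised. Here there are six of them. The plan draws its precision from about 100 HSAs, or from children grouped by HSA.

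HSAs in the same cluster are not obviously independent. They work in one area, attend the training workshops together and switch on the same date. Their outcomes are read from records at facilities in their catchment, and the Data management section itself says that location may affect record quality. A local outbreak, stock-out or lapse in record keeping that moves a whole cluster in some weeks would be counted up to 17 times as separate evidence. Because every HSA in a cluster switches together, such a movement falls directly on the control-versus-intervention contrast.

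At stake are the p-value and confidence interval for every main outcome.

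**Working it through.** **1. The plan's own figure.** The protocol names a paired calculation but no discordance pattern. I assume that all discordance runs in one direction. With paired change d, one-sided alpha 0.05 and 80% power:

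n = [(1.645·√d + 0.842·√(d − d²)) / d]²

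This gives n = 100.9 at d = 0.06, 93.0 at 0.065 and 86.2 at 0.07. The stated 97 HSAs for a 6–7 point change lies inside this range. The match counts each HSA as one independent unit; the six clusters do not enter.

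**2. Inputs for the error rate.** From the protocol:

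- 6 clusters and 102 HSAs, so 102/6 = 17 HSAs per cluster.
- 2 to 7 weeks in each phase (Data collection).
- 10 children per HSA per week (Recruitment).
- A 1% control referral rate (Sample size).

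Assumed:

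- One cluster crosses per step, so control weeks are 2, 3, 4, 5, 6, 7 and each cluster has 9 weeks in total. The design figure is not shown.
- A cluster-by-week coefficient of variation (CV) of 20%, 30% or 50%, and an HSA CV of 50%.

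This layout gives 102 × 9 × 10 = 9,180 children, somewhat more than the 8,000 planned.

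**3. HSA-level paired comparison, no true effect.** The HSA's own level cancels. The share of the variance of an HSA's change that is common to its cluster is

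ρ = (CV·p)² / [(CV·p)² + p(1 − p)/10]

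The design effect is 1 + 16ρ, and the true two-sided error is about 2·[1 − Φ(1.96/√(1 + 16ρ))].

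| Rate p | CV | ρ | Design effect | Error, formula | Error, simulated |
|---|---|---|---|---|---|
| 1% | 20% | 0.004 | 1.06 | 6% | 6–8% |
| 1% | 30% | 0.009 | 1.14 | 7% | 6–7% |
| 1% | 50% | 0.025 | 1.39 | 10% | 10–11% |
| 5% | 20% | 0.021 | 1.33 | 9% | 8–9% |
| 5% | 30% | 0.045 | 1.72 | 14% | 14% |
| 5% | 50% | 0.116 | 2.86 | 25% | 25% |
| 10% | 20% | 0.043 | 1.68 | 13% | 14% |
| 10% | 30% | 0.091 | 2.45 | 21% | 20–24% |
| 10% | 50% | 0.217 | 4.48 | 35% | 36–39% |

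A repeat simulation (3,000 trials per setting) gave 5%, 7% and 9% at the 1% rate, 8%, 14% and 24% at 5%, and 13%, 21% and 36% at 10%. With no cluster-by-week variation the error was about 5%. A t-test on the six cluster means stayed near 5% throughout.

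**4. z-test on pooled children.** Each phase totals 2+3+4+5+6+7 = 27 cluster-weeks, or 27 × 170 = 4,590 children. Early and late clusters contribute unequally to the two phases. The weights on the cluster means are ±5/27, ±3/27 and ±1/27, so the between-cluster SD enters with factor √(70)/27 = 0.31. With no cluster-by-week variation, simulation gives:

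- Stable cluster rates differing with an assumed CV of 30%: rejection about 7%, 19% and 28% at rates of 1%, 5% and 10%.
- No stable differences between clusters: about 6%, 6% and 9%.

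Check at a 5% rate and 30% CV. The binomial SE is √(2 × 0.05 × 0.95/4,590) = 0.00455. The cluster part is 0.31 × 0.015 = 0.00465. The HSA part is 0.31 × 0.025/√17 = 0.00188. The variance ratio is 1 + (0.00465² + 0.00188²)/0.00455² ≈ 2.21, which gives an error of about 19%.

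**5. Power on six clusters.** Take an effect that gives 80% one-sided power with 97 independent HSAs. A t-test on six cluster means has power of about 71%, 61%, 50% and 39% at ρ = 0, 0.02, 0.05 and 0.10.

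**The case against.** Five objections deserve weight.

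- **Children.** A reader might infer that the plan treats single children as independent throughout. It does not: the secondary model adjusts for HSA. Children are treated as independent only if the z or chi-square tests pool them, and the protocol labels those tests unadjusted.
- **Wrong standard errors.** A reader might also infer that the standard errors are certainly wrong. If no change over time were shared within clusters, HSA-level paired standard errors would be valid. The protocol gives no figure either way.
- **The primary outcome.** At the 1% control referral rate the inflation is modest, about 6–8% for a CV of 20–30%. The larger figures need rates of 5–10%. The protocol expects 7–8% referral only under the intervention and gives no re-consultation rate. All three points stand and limit the claim.
- **Covariates.** Location and distance adjust for some stable geography. They do not capture shared change over time, so this answers little.
- **The SAP.** The protocol promises a full SAP before analysis, and small-sample detail may properly sit there. But the protocol already names the unit of analysis, the tests and the only cluster variable. Those are stated choices that a SAP following this text would inherit.

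**Conclusion.** The point holds in conditional form. The protocol randomises six clusters and fixes analyses that never use them, so the nominal 5% error is not protected. For an HSA-level paired test the true error is about 6–11% at a 1% rate, 8–25% at 5% and 14–39% at 10%. These ranges assume a cluster-by-week CV of 20–50%, an HSA CV of 50% and one cluster crossing per step. Pooled z-tests add a further problem that depends on how far stable cluster rates differ.

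The documents do not support saying that the urgent-referral result would be badly misleading at its assumed 1% control rate, nor that re-consultation is affected by any particular amount. A calendar trend is a separate source of bias; using the randomised cluster does not by itself remove it.

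**What to change.** Make the randomised geographic cluster the top level of inference, with HSA nested in cluster and a period term. Take the primary p-value and interval from a permutation test over the crossover orders that the design allowed. If one cluster crosses per step there are 6! = 720 orders, and the smallest p is 1/720, about 0.0014. Another small-sample method suited to six clusters would also serve. At a 1% rate a cluster-week holds only about 17 × 10 × 0.01 = 1.7 referrals, so cluster-by-week random effects would be weakly estimated; this favours permutation. Keep the z and chi-square results as description.

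The change affects analysis wording and code and needs no new data. The cost is wider intervals. The 80% power stated for 97 independent HSAs should also be restated on six clusters over a range of assumed correlations.
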